### Safety, tolerability, and blinding assessment

Adverse effects will be assessed using a questionnaire adapted from Antal et al. (59). Participants will be asked to complete the questionnaire after each session. The questionnaire includes items related to potential adverse effects such as headache, tingling, skin redness, neck pain, scalp pain, itching, drowsiness, difficulty concentrating, burning sensation, and acute mood change. In addition, other information regarding when the adverse event occurred, its duration, and where the discomfort is located will be recorded. Participants will quantify the severity of adverse effects as follows: (0) absent; (1) mild; (2) moderate; and (3) severe.

The questionnaire will also inquire about participants’ perception of whether they received active stimulation or not. For more details, see Supplementary materials S4.

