### Sample size

The sample size is calculated on the primary outcome by *a priori* analysis in G*Power, version 3.1.9.7 (The G*Power Team, Düsseldorf, Germany). Based on the study design and assumptions, the estimated results suggest that participants who receive a single session of active tDCS or hf-tRNS will demonstrate an improvement in TEXT reading accuracy compared to their baseline performance. On the other hand, participants who receive a single session of sham tDCS or sham tRNS are not expected to show a significant change in their performance compared to baseline. While the design of this project has never been employed in DD, we will refer to (i) a previous study by Costanzo and collaborators (16) who prove the effectiveness of a one-session active left anodal/right cathodal tDCS over temporo-parietal regions in a within-subject design; (ii) a study with similar features (e.g., one-session, sham-controlled experiment, comparing baseline vs. tDCS vs. tRNS vs. sham) assessing other cognitive functions (35).

Based on these previous results, to be cautious and conservative, we estimate a medium effect size (f) of 0.25. With an estimated *f* = 0.25, α value = 0.05 (i.e., probability of false positives of 5%), and *β* = 0.80 (i.e., at least 80% power), the sample size is 24 as calculated using a Repeated Measures-Analysis of Variance (RM-ANOVA) model with four within factors (i.e., baseline, active tDCS, active hf-tRNS, and sham).

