### Statistical analyses and expected results

The Shapiro–Wilk test will be used to test the normality of the data and Levene’s test for the homogeneity of variances. When data will be normally distributed and the assumption of homogeneity will not be violated, parametric analyses will be computed. When one assumption will not be met, non-parametric tests will be conducted or a log-transformation of the distribution will be applied. Sphericity will be verified by Mauchly’s sphericity test and when not met, Greenhouse–Geisser correction will be applied.

Chi-Square analyses will be used to compare the groups on demographic and safety and blinding measures (categorical variables).

Covarying for age, a preliminary analysis to test the effect of the four repetitions (Day 0, Day 1, Day 2, and Day 3) of the reading tasks (accuracy and speed of TEXT, HF, LF, and NW) will be conducted.

RM-ANOVA will be used to compare reading measures (TEXT, HF, LF, and NW accuracy and speed), separately, with conditions (Day 0, A, B, C) as a within-subjects factor and age as covariate.

*Post hoc* comparisons will be assessed using Tukey’s honest significance test.

Partial eta squares (η_p_^2^) will be used as measures of effect sizes.

We hypothesize that:

hf-tRNS will be at least as effective as tDCS in improving TEXT reading accuracy compared with sham condition (primary outcome);hf-tRNS and tDCS will improve performance in the remaining reading tasks (TEXT reading speed and HF, LF, and NW reading accuracy and speed) compared with sham condition;hf-tRNS and tDCS will be as safe as sham condition (i.e., neither tDCS nor hf-tRNS will induce severe AEs or lead to dropouts due to intolerance to stimulation);the blinding will be kept across the conditions.

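### The hypothesis that blinding is kept is a no-difference claim, but the only analysis named for it is an unpaired chi-square difference test in 24 children, where non-significance is weak evidence

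*Protocol article*

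**What the plan says.** The protocol article, under Statistical analyses and expected results, lists four hypotheses. The last is that "the blinding will be kept across the conditions". For its analysis the same section offers one sentence: "Chi-Square analyses will be used to compare the groups on demographic and safety and blinding measures (categorical variables)". It names no bound on the difference, no interval and no blinding index.

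The data are described under Safety, tolerability, and blinding assessment. The questionnaire completed after each session will "inquire about participants’ perception of whether they received active stimulation or not". Under Study design, every child has an active tDCS, an active hf-tRNS and a sham session, so each child contributes three answers.

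The Sample size section sizes the trial for something else. It opens "The sample size is calculated on the primary outcome by" an a priori power analysis, says "we estimate a medium effect size (f) of 0.25" with alpha 0.05 and "i.e., at least 80% power", and concludes that "the sample size is 24 as calculated using a Repeated Measures-Analysis of Variance (RM-ANOVA) model with four within factors". No power is stated for the blinding comparison.

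**The concern.** The claim and the tool point in opposite directions. A difference test can show that guesses differ between conditions. It cannot show that they do not, least of all in a sample sized for a reading outcome. Moving to a paired test would respect the design but would leave this problem in place.

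The stake is how the sham comparison is read. The primary outcome, text reading accuracy, depends on performance, and each child can compare three sessions, one of which delivers current only for a short turn-on period. The Introduction and Discussion cite evidence that tRNS is less perceptible than tDCS and blinds better, so unequal guessing is foreseeable. If children recognise active sessions, expectation could produce part of an active-versus-sham difference. An unwarranted statement that blinding held would encourage reading all of it as a stimulation effect.

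**Working it through.** **Inputs from the article.** N = 24, alpha 0.05 (stated for the sample size, assumed two-sided for the blinding test), one active-or-not answer per child per condition, three conditions. Withdrawn children are excluded and replaced, so about 24 complete sets are expected. The article gives no guess rates and no within-child correlation, so both are assumptions below.

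**The plan's own figure.** For a one-group repeated-measures ANOVA with m = 4 measurements, the noncentrality is λ = f²·N·m/(1 − ρ). Assuming ρ = 0.5 and sphericity, which the article does not state, λ = 0.0625 × 24 × 4 / 0.5 = 12 on (3, 69) df, with power 0.817. N = 23 gives 0.797. The stated 24 therefore reproduces, for the reading outcome only. Other correlations give N = 45 (ρ = 0), 32 (0.3) and 15 (0.7).

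**Three-condition paired test.** Simulated trials with latent-normal correlated binary answers, latent correlation 0 to 0.5, analysed by Cochran's Q = (k − 1)[kΣCⱼ² − T²] / [kT − ΣRᵢ²] with k = 3, on 2 df. Here Cⱼ are condition totals, Rᵢ child totals and T the grand total.

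| Assumed % guessing active (tDCS/hf-tRNS/sham) | Trials in which Q is not significant |
|---|---|
| 70/70/50 | 60–71% |
| 75/60/50 | 53–66% |
| 75/75/50 | 40–55% |
| 70/70/40 | 25–42% |
| 80/80/50 | 21–37% |
| 80/80/40 | 4–13% |

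The named chi-square (3 × 2, 2 df) misses 70–77% at 70/70/50, 65–72% at 75/60/50 and 54–58% at 75/75/50.

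**One pair of conditions.** Exact McNemar with 24 pairs. For 70% against 40%, P(both active) = 0.28 + φ√(0.21 × 0.24). At φ = 0 / 0.2 / 0.4 the discordant probabilities are 0.42 and 0.12, 0.375 and 0.075, and 0.330 and 0.030. Power is 42 / 51 / 64%, so 36–58% of trials miss a 30-point gap. For 60% against 40% the miss rate is 73–81%, for 70% against 30% it is 6–30%, and for 75% against 25% it is under 10%.

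**Behaviour of the chi-square when nothing differs.** With all true rates at 50%, the nominal 5% test rejects in about 2.4% of simulated trials at latent correlation 0.3 and 1.2% at 0.5. The standard error it uses is too large for positively correlated answers.

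**What an interval would show.** For a true difference of zero and guess rates of 50%, the 95% half-width is 1.96√[2 × 0.25 × (1 − φ)/24] = 0.283 / 0.253 / 0.219 at φ = 0 / 0.2 / 0.4, or about 22–28 points. To show equivalence within 20 points (two one-sided tests at 0.05, 80% power, true difference zero), n = 0.5(1 − φ)[(1.645 + 1.282)/0.20]², about 108 children at φ = 0 and 65 at φ = 0.4.

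**The case against.** The strongest reply has four parts.

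- **The article is condensed.** A margin, interval or blinding index might sit in a full protocol or analysis plan that is not shown. This has some force, and the point does not rest on their absence. It rests on the mismatch between the claim and the test, both of which the article states.
- **No decision rule is written.** A reader might infer that non-significance is the only way the investigators could conclude that blinding held. The article does not say so. It sets out a hypothesis and a test, and naming a chi-square does not rule out reporting intervals as well. What can be said is that it states no other route.
- **The miss rate depends on the assumed gap.** A reader might infer that the trial would overlook substantial unblinding about half the time. The documents neither define substantial nor give guess rates. About half fits a gap near 25 points. Larger gaps are usually found and smaller ones usually missed. This objection stands, so the results are shown as a range.
- **Blinding is a supporting hypothesis in a proof-of-concept study.** The primary analysis does not depend on this test. That is true and limits the severity, though the interpretation of the sham contrast does depend on blinding.

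Two further cautions also stand. The article does not define blinding kept, which could mean guessing no better than chance rather than equal guessing across conditions. And answers given after a session may partly reflect how well the child felt they read, not only recognition of the current. Changing the analysis does not resolve that second ambiguity.

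**Conclusion.** The point holds in a limited form. The article pairs a no-difference hypothesis with a difference test, in a sample sized for another outcome. A non-significant result could not carry the conclusion that blinding was kept.

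The size depends on assumed guess rates and correlations. With Cochran's Q, the chance of missing a real difference runs from about 60–71% (70/70/50%) down to 4–13% (80/80/40%), and no single figure describes it. The chi-square as named adds a second fault that does not depend on any assumed gap: it treats three answers from one child as independent. If those answers are positively correlated it rejects too rarely, and for a hypothesis supported by not rejecting, that errs in the favourable direction.

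The documents do not show that blinding will fail, nor that the investigators will read p > 0.05 as proof that it held. The matter should be corrected, but it does not undermine the primary analysis itself.

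**What to change.** In Statistical analyses and expected results, replace the chi-square for the blinding guess by three paired differences in the proportion guessing active: tDCS minus sham, hf-tRNS minus sham, and tDCS minus hf-tRNS, each with a 95% confidence interval from a method for paired proportions. The third contrast matters because the article itself expects the two techniques to differ in perceptibility.

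State that blinding will not be concluded from p > 0.05. Call it supported only if the intervals exclude a difference that the investigators choose and justify before unblinding. Otherwise report it as inconclusive.

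The cost is wording and analysis code, using the same questionnaire and the same children. The downside should be accepted openly. With half-widths of about 22–28 points, a bound of 20 points could not be met under these assumptions even if the observed difference were zero, so at N = 24 the likely statement is inconclusive.

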### Documentation, monitoring, and data management

The OPBG Contract Research Organization is responsible for designing the Case Report Form (CRF) and other data collection modules. The principal investigator must store all data for each subject. If any required data are missing, an explanation should be provided on the appropriate data collection forms and transcribed on the CRF page if necessary.

In case of clarifications, the investigator must respond within agreed timelines. Researchers will organize the retention of patient identification codes for a period of at least 15 years. Patient records must be retained for a minimum of 15 years.

The principal investigator will be the data custodian and will store the data at the Child and Adolescent Neuropsychiatry Unit. The subject data will be anonymized and coded. Paper records will be kept in a locked drawer, with the key held by the principal investigator. The database containing the coded data will have protected access, with the key also held by the principal investigator.

The investigator will allow monitoring, verification, review by the Institutional Review Board/Independent Ethics Committee, and inspection by regulatory authorities related to the study, providing direct access to original Data/Documents. The CRF and original documents can be consulted and verified by the clinical monitor and inspected by regulatory authorities at any time.

For all data that cannot be printed, their transcription on the patient’s study data collection folder will serve as the original record of such data. The obtained results will be provided to the participants and their parents or guardians at the conclusion of the experiment.

### Withdrawal of subjects and intervention modifications

Any suspensions or interruptions of the treatment will be documented by the investigator. Subjects will be immediately withdrawn from the study if there are foreseeable or unforeseeable adverse effects. If withdrawal occurs during the intervention phase, the subject’s data will not be considered for analysis. Replaced subjects will be those who undergo the complete protocol.

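### The withdrawal rule drops all data of children withdrawn for adverse effects, so the safety, tolerability and blinding comparisons omit those who tolerated stimulation worst

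*Protocol article*

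**What the plan says.** Three sentences in the section on withdrawal of subjects and intervention modifications act together:

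- Trigger: "Subjects will be immediately withdrawn from the study if there are foreseeable or unforeseeable adverse effects".
- Consequence: "If withdrawal occurs during the intervention phase, the subject’s data will not be considered for analysis".
- Replacement: "Replaced subjects will be those who undergo the complete protocol".

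The same section adds: "Any suspensions or interruptions of the treatment will be documented by the investigator". The data management section adds: "The principal investigator must store all data for each subject".

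Safety and blinding are assessed by a questionnaire after each session: "Participants will quantify the severity of adverse effects as follows: (0) absent; (1) mild; (2) moderate; and (3) severe". The statistical analyses section plans chi-square comparisons of the safety and blinding measures. Its safety hypothesis is that "neither tDCS nor hf-tRNS will induce severe AEs or lead to dropouts due to intolerance to stimulation". The Introduction says safety, tolerability and blinding will be compared between the two techniques, and the Discussion lists the safety and tolerability comparison among the main purposes.

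**The concern.** The exclusion covers the withdrawn child's data as a whole. It is not confined to reading scores, and no section of the article carves out safety, tolerability or blinding data.

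Because adverse effects trigger withdrawal, being left out of the analysis depends directly on the outcome that the safety analysis compares. Three things follow if the rule is applied as written:

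- Adverse-effect rates are understated.
- The contrast between tDCS, hf-tRNS and sham is distorted, in a direction set by whichever condition caused the withdrawals.
- The part of the safety hypothesis about intolerance dropouts is assessed in a set that by construction contains none.

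The blinding guesses of children who felt the stimulation most may be lost as well. The study is meant to inform which technique is safer and more suitable for children, so this bears on a main conclusion. It does not bear on text reading accuracy, the primary outcome.

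**Working it through.** **The plan's own figure.** The sample size section gives 24 children from f = 0.25, alpha = 0.05, 80% power and four repeated measurements. I used noncentrality f² × n × m/(1 − ρ) with m = 4 and degrees of freedom 3 and 3(n − 1). The article states neither the correlation ρ nor the sphericity parameter. Assuming ρ = 0.5 and sphericity, power is 0.797 at n = 23 and 0.817 at n = 24, so 24 is reproduced. With ρ = 0 the same formula needs 45 children and with ρ = 0.7 it needs 15. Nothing below depends on this choice. The 24 are completers, and the fix leaves that number alone.

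**Inputs for the illustrations.** The 24 completers come from the sample size section. The numbers of withdrawals, the withdrawal risks and the completers' adverse-effect counts are assumptions, because the article gives none.

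**1. Dropouts seen and dropouts that occurred.** Suppose k children are withdrawn for intolerance and replaced until 24 complete. The analysed set shows 0/24 whatever k is (exact 95% upper limit 1 − 0.025^(1/24) = 14.2%). All treated children show k/(24 + k):

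| k | Analysed set | All treated | Exact 95% CI, all treated |
|---|---|---|---|
| 1 | 0/24 | 1/25 = 4.0% | 0.1–20.4% |
| 2 | 0/24 | 2/26 = 7.7% | 0.9–25.1% |
| 3 | 0/24 | 3/27 = 11.1% | 2.4–29.2% |

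**2. How often this would arise.** Let w be the risk per child of withdrawal for intolerance, recruiting until 24 complete. P(at least one) = 1 − (1 − w)^24, and the expected number is 24w/(1 − w):

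| Assumed w | P(at least one) | Expected withdrawals |
|---|---|---|
| 2% | 38% | 0.5 |
| 5% | 71% | 1.3 |
| 10% | 92% | 2.7 |

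The analysed set shows none in every case.

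**3. Direction of the bias.** Suppose completers report an effect in 3/24 tDCS sessions and 2/24 hf-tRNS sessions: 12.5% − 8.3% = +4.2 points. These counts were chosen to lie near the 13% and 7% of sessions with itching that the Discussion reports from a comparative study in children. Add k children withdrawn on Day 1, all under one condition:

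| k | Analysed set | All treated, withdrawn under tDCS: (3 + k)/(24 + k) − 2/24 | All treated, withdrawn under hf-tRNS: 3/24 − (2 + k)/(24 + k) |
|---|---|---|---|
| 1 | +4.2 | 4/25 − 2/24 = +7.7 | 3/24 − 3/25 = +0.5 |
| 3 | +4.2 | 6/27 − 2/24 = +13.9 | 3/24 − 5/27 = −6.0 |

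If the three withdrawals fall on Day 3, after two sessions without the effect, the all-treated differences are 6/27 − 2/27 = +14.8 and 3/27 − 5/27 = −7.4 points. The analysed set shows +4.2 throughout, even where the all-treated difference has the opposite sign.

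**The case against.** The strongest reply is that the withdrawal section should be read with the rest of the article. Taken fully literally, any tingling would end participation, and the 0–3 severity scale and the safety comparison would have almost nothing to work on. If the trigger is read sensibly, the exclusion should be too: it serves the complete-case repeated-measures ANOVA, which needs every condition from 24 children. The safety hypothesis itself treats dropouts as a result, so someone must count them. One documented intolerance dropout would refute it, and interruptions are documented and data stored.

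That narrower reading is possible, but the text does not state it. An analyst following the sentence would drop the safety records too. Storing and documenting data does not bring them into an analysis, and the sentence says they are left out. A descriptive dropout count could still be given, but none is planned. Reading the trigger more literally only makes the loss larger.

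Some points do stand:

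- The severity scale suggests that mild effects will not usually end participation, so few children may be lost.
- The section on protection of risks halts stimulation for scalp discomfort or headache without saying that the child is withdrawn, so who would be withdrawn is not fully clear.
- The replacement sentence is loosely worded, although replacement by completers is its natural meaning.
- The largest shifts above need all three withdrawals under one condition. Even then an uncorrected, unpaired chi-square test does not reach 5%: p = 0.64 for 3/24 v 2/24, 0.17 for 6/27 v 2/24, and 0.56 for 3/24 v 5/27. The damage is to the reported rates and their direction, not to a significance call.

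It could also be said that safety populations belong in the full protocol or analysis plan. The point here is not a missing definition. It is an explicit rule that conflicts with the article's own safety aim.

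**Conclusion.** The concern holds and should be fixed. As written, the rule excludes children from the safety, tolerability and blinding comparisons because of how badly they tolerated stimulation, and the analysed set cannot show an intolerance dropout whatever the true rate. In the illustrations, one to three withdrawals mean 4.0% to 11.1% of treated children go unseen. Three withdrawals under one condition move the tDCS minus hf-tRNS difference from +4.2 points to +13.9 or −6.0.

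These sizes rest on assumed withdrawal numbers, withdrawal risks and adverse-effect counts. The conclusion about the rule rests on the text alone, with medium confidence because a narrower intention is possible. There is no effect if nobody withdraws.

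**What to change.** Amend the withdrawal section as follows:

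- Limit the exclusion sentence, and replacement, to the complete-case repeated-measures ANOVA of reading.
- State that adverse-effect, tolerability and available blinding data of every child who starts at least one stimulation session are analysed under the condition received.
- State that withdrawals and halted sessions are reported by condition over all treated children. In these analyses replacements are added to the withdrawn children, not substituted for them.

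Optionally, a mixed model that keeps the completed reading sessions of withdrawn children could serve as a sensitivity analysis. The fix does not depend on it.

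The cost is a wording amendment, with the prior favourable ethics opinion that the section on study conclusion requires for any modification. No new data are needed: the questionnaire, data storage and documentation of interruptions are already provided for. The reading analysis keeps its 24 completers. The price is slightly unequal numbers per condition and a less tidy safety table.

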### Early conclusion or suspension of the study

The promotor may terminate the study at any time and promptly notify the investigators and ethics committee. Patients will be examined as soon as possible and will continue to be followed according to normal clinical practice.

